### Statistical analysis methods

1. **Homogeneity Analysis:** Baseline comparison analysis of demographic and clinical characteristics of the participants enrolled in each group will be conducted to assess comparability between groups.
2. **Efficacy Analysis:** Statistical analyses of the primary and secondary efficacy end points will be performed based on the FAS for comparisons between groups.
3. **Safety Analysis:** The incidence of AEs and AEs related to the study drug will be compared between groups. A tabular description will be provided for AEs occurring during the trial, changes in laboratory test results (normal/abnormal) before and after the trial, and the relationship between abnormal changes and the study drug.
4. **Overall participant profile:** For the overall information of participants, a flowchart was used to describe the total number of screened individuals, reasons for screen failures, randomized participants, those who received treatment, and those who discontinued or were excluded, along with detailed explanations, and so on. Specific descriptions of screening, randomization and enrollment condition, together with the details of those who failed to pass the screening, were further reported in the following step. Finally, the overall completion and incomplete status of participants from the experimental and control group, and detailed information about each participant who did not complete the experiment were described respectively.
5. **Demographic and clinical characteristics of participants at baseline:** Baseline demographic and clinical characteristics was analyzed to assess comparability between the groups, beginning with statistical description. Continuous variables were summarized using means, medians, standard deviations, quartiles, and ranges. Normality was tested, followed by between-group comparisons via t-tests for normally distributed data or Wilcoxon rank-sum tests for nonparametric data. Categorical and ordinal variables will be expressed as frequencies and percentages, analyzed with chi-square or Fisher’s exact tests.
6. **Analysis of Primary Efficacy Outcomes**

Response Rate: The proportion of participants with a reduction of ≥ 50% in MADRS scores at Weeks 4 and 8.

Clinical Remission Rate: The proportion of participants with a MADRS score ≤ 10 at Weeks 4 and 8.

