## Exclusion criteria

1. Any other DSM-5 psychiatric disorder other than generalized anxiety disorder and social anxiety disorder diagnosed at present or lifetime;

2. Subjects with serious suicide ideation or attempts;

3. Subjects who have received treatments with adjunctive antidepressants and/or antipsychotic medications in the current depressive episode (small doses of benzodiazepines were permitted);

4. Subjects who have received non-drug treatments in past 6 months for more than 10 times, such as electroconvulsive therapy (ECT), repetitive transcranial magnetic stimulation (rTMS), and systemic psychotherapy;

5. DSM-5 alcohol or drug dependence;

6. History of head injury or loss of consciousness for more than 5 minutes;

7. Subjects with a history or current diagnose of major physical illness (such as thyroid disease, lupus erythematosus, diabetes, lung, liver and kidney damage, infection, major trauma and etc.);

8. Pregnant or breast-feeding;

9. Epilepsy, history of seizures or family history of epilepsy;

10. Receiving hormone therapy at present;

11. Transaminases (ALT or AST) 2 times or more above the upper limit of normal range;

12. QTc >= 430 msec (for males) or >= 450 msec (for females) in ECG;

1. Any subject with some other conditions that the researchers believe may affect the study results.

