## Termination of study intervention

If intolerable AEs occur in participants, or if AEs that the investigator deems may increase the risk to participants are observed, the use of investigational medication should be discontinued. The reasons and timing for the discontinuation of the intervention should be documented in detail.

Discontinuation of the study intervention does not mean discontinuation of the study itself. Participants should continue to follow the procedures outlined in the study protocol. If clinically significant changes in the laboratory tests occur after enrollment (including but not limited to deviations from baseline levels), the investigator or a qualified designated person will determine whether changes in participant management are necessary. Any new clinically relevant findings will be reported as AEs.

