## Safety assessments

The safety profile of perospirone as an adjunctive antidepressant treatment for MDD will be comprehensively evaluated using the TESS and the incidence of AEs.

The TESS include symptoms and signs of common AEs, as well as several laboratory test results. Each symptom will be assessed in terms of AE severity, the relationship between AEs and investigational medications, and the corresponding management measures.

The evaluation of AEs incidences will include both the overall incidence of AEs and specific incidences related to liver and kidney function, electrocardiogram (ECG) abnormalities, and other relevant aspects. This assessment will involve monitoring and recording all AEs and SAEs, routine blood and biochemical parameters, vital signs, physical examinations, and all treatment methods and concomitant medications. Safety indicators will encompass vital signs, physical examinations, clinical laboratory parameters, AEs, and reasons for early withdrawal. For vital signs and laboratory parameters, the proportion of abnormal test results will be compared between the study group and the control group.

The incidence of AEs will be expressed as the ratio of participants experiencing AEs during the trial to the total number of participants eligible for safety evaluation. AEs will be summarized according to treatment group, body system, and events within each system.

The assessment of AEs includes classification, grading, relationship to the medications, management measures, and outcomes.

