## Adverse event (AE) and serious adverse event (SAE)

### Definition of adverse event (AE)

An Adverse event (AE) is defined as any untoward medical occurrence in a participant associated with the use of the study medication or occurring during the study, regardless of whether there is a causal relationship with the study medication or treatment process.

Endpoint events are not considered AEs unless, based on the investigator's best clinical judgment, considering the course, severity, or other characteristics of the event, it should be regarded as an exception in this clinical context.

Any AE, regardless of its severity or whether it is related to the study medication, should be recorded in the CRF from the time the participant signs the informed consent form until the end of the last scheduled visit as planned in the study protocol. The investigator should specifically describe the timing of the event, its severity, any actions taken regarding the study medication, symptomatic treatment provided, outcomes, and his/her judgment on whether the AE might have been caused by the study medication.

Laboratory test results, vital signs, or ECG abnormalities will be recorded as AEs if they are medically related to the study medication, such as when accompanied by clinical symptoms, necessitating symptomatic treatment, leading to discontinuation of the medication, or resulting in serious consequences.

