### Requirements for AE recording and follow-up

When participants receiving medical services during visits or monitors conducting reviews, the occurrence of AEs or SAEs should draw the attention of researchers.

All AEs that do not meet the criteria for SAEs will be recorded in the CRF, including both local and systemic reactions. Information to be collected includes a description of the event, onset time, assessment of severity by a physician, relationship to the investigational medication (which can only be assessed by trained personnel with diagnostic authority), and the time when the event is resolved or stabilized. All AEs occurring during the study must be comprehensively documented, regardless of their relationship to the study intervention. All AEs should be followed up until reasonably resolved.

Medical conditions at the time of participant screening should be considered baseline and not reported as AEs. However, if the participant's condition worsens at any time, it should be recorded as an AE.

Changes in the severity of AEs should be documented to assess the duration of the event at different severity levels. Intermittent AEs require recording of onset time and the duration of each onset.

From the time of signing the informed consent form to the end of the trial, investigators should record all AEs/SAEs. At each visit, researchers should inquire about AEs/SAEs that occurred since the last visit and follow up on the outcome of the events until they are resolved or stabilized.

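### The only laboratory summaries the protocol states are two-category, so they do not show how large an ALT or AST rise is, and the between-arm comparison ignores baseline status

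*Protocol*

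**What the plan says.** Two places in the protocol state how laboratory values are summarised.

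- Section 9.2.4, item 3 (Safety Analysis) promises a tabular description of "changes in laboratory test results (normal/abnormal) before and after the trial", together with "the relationship between abnormal changes and the study drug".
- Section 8.2 (Safety assessments) says: "For vital signs and laboratory parameters, the proportion of abnormal test results will be compared between the study group and the control group".

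Section 12, item 5, which gives the adjusted statistical methods, compares adverse event rates and states no further laboratory summary.

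Two exclusion criteria in section 5.2 bear on who can enter with a raised transaminase. Criterion 11 excludes "Transaminases (ALT or AST) 2 times or more above the upper limit of normal range", so a value above normal but below that cut-off is allowed. Criterion 7 excludes major physical illness, including "liver and kidney damage, infection, major trauma and etc".

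Section 2.2.1 reports raised ALT in 13 of 381 patients (3.4%) in the pre-approval studies, and the same for AST. The endpoint table in section 3 includes liver function in the safety endpoint. The schedule in section 1.3 has liver function tested at baseline and at weeks 2, 4 and 8.

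**The concern.** A two-category summary records which side of a limit a value lies on. It does not record how far beyond the limit the value went. For transaminases the distance matters clinically: a value just over the limit and one ten times the limit fall in the same cell.

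Exclusion 11 adds a second difficulty. If the limit is the ULN, a patient admitted with a mildly raised value is already in the abnormal category. No later change, except a return to normal, can move that patient to another cell.

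The section 8.2 comparison has a further weakness. As worded it takes the proportion abnormal without reference to where the patient started, so abnormality present at entry and abnormality arising on treatment are added together.

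At stake is how informatively a named drug effect is reported. No efficacy result and no powered test is involved.

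**Working it through.** **Reproducing the protocol's figure.** 13/381 = 3.41%, which agrees with the stated 3.4%. The exact (Clopper-Pearson) 95% interval is 1.83% to 5.76%.

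**What the two categories hide.** The values below are illustrative, in multiples of ULN. The cut at 1 x ULN is an assumption, because the protocol does not define abnormal.

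| Baseline | Post-baseline | Fold change | Cell |
|---|---|---|---|
| 0.8 | 1.1 | 1.38 | normal to abnormal |
| 0.8 | 10 | 12.5 | normal to abnormal |
| 1.5 | 1.5 | 1.00 | abnormal to abnormal |
| 1.9 | 3.1 | 1.63 | abnormal to abnormal |
| 1.9 | 10 | 5.26 | abnormal to abnormal |
| 1.9 | 1.1 | 0.58 | abnormal to abnormal |

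The first two rows are indistinguishable, and so are the last four. The first pair affects any patient with a rise; the last four concern only patients raised at entry.

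**How many patients.** Assume the section 2.2.1 rate carries over and reflects new rises; that section does not say baseline values were normal. With 108 patients randomised to perospirone (section 1.1; the safety set may be slightly smaller), 108 x 0.0341 = 3.7 would have a raised ALT (interval 2.0 to 6.2), and likewise AST.

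The share entering above normal, b, is not given. I take 2% to 15% as an assumed range; exclusion 7 pushes it down by an unknown amount.

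- Raised at entry: 108b = 2.2 to 16.2 on perospirone and 102b = 2.0 to 15.3 on placebo.
- Raised at entry and rising, if the two are independent: 108 x b x 0.0341 = 0.07 at b = 2% and 0.55 at b = 15%, so usually none or one.

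**Effect on the section 8.2 comparison.** Count patients, let those raised at entry stay abnormal, take p = 0.0341 for new rises on perospirone, and assume q = 0.01 on placebo (the documents give no placebo rate).

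- Pre-existing share of the perospirone count: b / (b + (1 - b)p)
- Ratio between arms: (b + (1 - b)p) / (b + (1 - b)q), against p/q = 3.41 without dilution
- Risk difference: (1 - b)(p - q), against 2.41 points without dilution

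| b (assumed) | Pre-existing share | Ratio | Difference (points) |
|---|---|---|---|
| 2% | 37% | 1.79 | 2.36 |
| 5% | 61% | 1.39 | 2.29 |
| 15% | 84% | 1.13 | 2.05 |

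The ratio shrinks markedly; the risk difference loses at most about 0.4 points (2.41 - 2.05 = 0.36).

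**The case against.** The strongest reply is that banded tables and change-from-baseline listings are detail for a statistical analysis plan, which may exist and may add them. The protocol does not call its tables exhaustive, and the numeric values are collected at every visit. This has weight: nothing is lost from the data. But the protocol is not silent here. It names a two-category form twice, and that stated form is what needs changing.

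A reader might infer that the trial would be blind to liver injury in patients raised at entry. The documents do not support that. Section 8.4.6 says that if the participant's "condition worsens at any time, it should be recorded as an AE". Section 7.1 deals with "clinically significant changes in the laboratory tests occur after enrollment (including but not limited to deviations from baseline levels", and has new clinically relevant findings reported as adverse events. Section 8.4.1 says: "Laboratory test results, vital signs, or ECG abnormalities will be recorded as AEs if they are medically related to the study medication". Section 8.4.3 grades adverse events on five general CTCAE levels, and section 9.2.4 evaluates severity and presents all of them in a table. A clinically important rise therefore has a route to a reported severity grade. That route depends on judgement, and section 8.4.6 does not say whether an isolated enzyme value is a condition. It yields a grade but no ULN multiple. The Treatment-Emergent Symptom Scale is a further possible route. It covers only some laboratory tests, the protocol does not say that ALT or AST is among them, and section 9.2.3 counts its items as zero versus above zero.

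A reader might also infer that section 8.2 presents pre-existing abnormality as treatment-emergent. It does not say so. It gives no time point, and it speaks of test results rather than patients. The before/after table in section 9.2.4 can itself separate new from pre-existing abnormality. What stands is that the section 8.2 comparison, taken alone, does not account for baseline.

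Finally, abnormal is undefined. If it meant clinically significant, a mildly raised entry value could count as normal and a later rise would show as a change of category. The part of the point about patients raised at entry therefore rests on a cut at the ULN.

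**Conclusion.** The point holds, at minor severity. The stated laboratory summaries are two-category and, with abnormal read as above the ULN, do not show the size of an ALT or AST rise in any patient. That is the firm part, and it concerns about 3.7 of 108 perospirone patients for ALT if the pre-approval rate applies. The inability to see a rise in a patient already raised at entry follows from the same reading but touches few people, with 0.07 to 0.55 expected in the perospirone arm under the assumed entry range.

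The ratio figures for section 8.2 should not be read as a forecast, because they depend on an assumed entry prevalence and an assumed 1% placebo rate. Nor do they show bias between arms: randomisation makes the share raised at entry equal in expectation, so counting those patients mainly adds noise. The effect is confined to descriptive safety reporting.

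**What to change.** In section 9.2.4, item 3, repeated in section 12, item 5, add for ALT and AST:

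- a by-arm table in the safety set of baseline category against worst post-baseline category over all visits, in ULN multiples (for example ≤1, >1 to <3, 3 to <5, ≥5, collapsed where cells are sparse);
- descriptive change from baseline by visit.

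In section 8.2, make the laboratory comparison the proportion of patients normal at baseline who become abnormal at any post-baseline visit.

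The cost is some wording and a few extra tables from tests already scheduled. With so few expected rises, some cells will be sparse. The bands are a suggestion, since the protocol gives none.

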## Regulatory, ethical, and study oversight considerations

### Informed consent process

Informed consent is a process that begins before an individual agrees to participate in a study and continues throughout their involvement in the research. The informed consent document will be approved by the Institutional Review Board (IRB), and participants will be asked to read and review it. The investigator will explain the study to the participant and answer any questions they may have. The investigator will orally explain to the participant, in a manner that they can understand, the purpose of the study, the procedures involved, potential risks, and the rights of the participant. Before signing the written informed consent, the participant should be given ample time to read carefully and ask questions. The participant should have the opportunity to discuss the study with family members or representatives or to reflect on it themselves before agreeing to participate. The participant will sign the informed consent document before any study-related procedures are conducted. The participant must be informed that participation in the study is voluntary and that they can withdraw from the study at any time without penalty. The investigator will provide the participant with a copy of the informed consent document for their records. The informed consent process should be conducted before the participant undergoes any study-related procedures, and the process (including the date) should be documented in the source documents, along with the retention of the signed informed consent form. The investigator must specifically inform the participant that "if they choose not to participate in this study, their quality of medical care will not be adversely affected," to ensure the rights and welfare of the participant.

### Suspension and termination of the study

If there are sufficient and reasonable grounds, this study may be temporarily suspended or prematurely terminated. The party deciding to suspend or terminate the study shall provide written notification to the participants, investigators, funding agencies, clinical trial sponsors, and regulatory authorities, and document the reasons for the suspension or termination of the study. If the study is prematurely terminated or suspended, the PI shall promptly notify the participants, the IRB, and the sponsor, and provide the reasons for the study termination or suspension. Where applicable, the investigator will contact the participants and inform them of changes to the visit schedule. Reasons for suspension or termination may include, but are not limited to:

1. Identification of unexpected, significant, or unacceptable risks to participants.
2. Non-compliance with the protocol requirements.
3. Incomplete data and/or data insufficient for evaluation.
4. Confirmation that the primary endpoint has been reached.
5. Determination that the study is futile.

The study may resume only after issues related to safety, protocol compliance, and data quality have been resolved and meet the requirements of the sponsor, the IRB, and/or the National Medical Products Administration (NMPA).

### Confidentiality and privacy

All investigators, staff, and sponsors involved in the study must strictly maintain confidentiality and protect the privacy rights of the participants. In addition to clinical information related to the participants, this confidentiality will extend to cover tests involving biological sample analysis and genetic testing. Therefore, the study protocol, documents, data, and all other information generated during the study will be kept strictly confidential. No study materials or data may be disclosed to unauthorized third parties without the written permission of the sponsor.

All research activities will be conducted in as private an environment as possible. Monitors of the study, other authorized representatives of the sponsor, representatives of the IRB, regulatory authorities, or representatives of the pharmaceutical company providing the study products may inspect all documents and records that the investigator is required to maintain, including but not limited to the medical records of the study participants (in offices, clinics, or hospitals) and pharmacy records. The clinical research center should allow access to these records. Contact information of the participants will be securely stored at each clinical research center for internal use during the study. At the end of the study, all records will continue to be kept at the sponsor's institution for five years after the publication of the results.

Participant study data used for statistical analysis and research reporting will be transferred and stored in the data management center. This does not include the participants' contact information or identifying details. Instead, individual participants and their study data will be identified through a unique study identification code. Research data entered by researchers at the clinical research center and the data management system used will be secured and password-protected. At the end of the study, all study databases will be de-identified and stored at the sponsor's institution.

### Future utilization of stored samples and data

The data collected in this study will be stored and analyzed in the data management center. Upon completion of the study, de-identified archival data will be transferred and stored by the sponsor for use by other researchers, including those outside this study. Permission to transfer data to other researchers will be included as part of the informed consent process.

With the consent of the participants and approval from the local IRB, biological samples that do not contain personal information will be stored at each participating center, with the same purpose as the shared data repository maintained by the sponsor. While maintaining the anonymity of participants' personal information, a code linking the stored biological samples to the phenotypic data of the source participants will be provided to each center.

During the course of the study, participants may choose to withdraw their consent for storing their biological samples for future research. However, after the study is completed, consent for the storage of biological samples may not be withdrawn.

Upon completion of the study, access to the study data and/or samples will be provided through the sponsor.

